## Abstract

**Background:**

Patients with a hemispheric infarct and massive space-occupying brain oedema have a poor prognosis. Despite maximal conservative treatment, the case fatality rate may be as high as 80%, and most survivors are left severely disabled. Non-randomised studies suggest that decompressive surgery reduces mortality substantially and improves functional outcome of survivors. This study is designed to compare the efficacy of decompressive surgery to improve functional outcome with that of conservative treatment in patients with space-occupying supratentorial infarction

**Methods:**

The study design is that of a multi-centre, randomised clinical trial, which will include 112 patients aged between 18 and 60 years with a large hemispheric infarct with space-occupying oedema that leads to a decrease in consciousness. Patients will be randomised to receive either decompressive surgery in combination with medical treatment or best medical treatment alone. Randomisation will be stratified for the intended mode of conservative treatment (intensive care or stroke unit care). The primary outcome measure will be functional outcome, as determined by the score on the modified Rankin Scale, at one year.

## Background

Large cerebral infarcts are commonly associated with variable degrees of brain oedema. In severe cases, this may lead to transtentorial or uncal herniation. Serious oedema formation usually manifests itself between the second and fifth day after stroke onset [1-4]. Brain tissue shifts rather than raised intracranial pressure (ICP) are probably the most likely cause of the initial decrease in consciousness [4,5].

Fatal space-occupying brain oedema is rare, and occurs in 1 to 5% of patients with a supratentorial infarct [6,7]. However, in younger patients with ischaemic stroke, herniation accounts for about half of the deaths in the first month [8]. Patients with a hemispheric infarct and massive space-occupying brain oedema have a poor prognosis: in recent intensive care (IC)-based prospective series, the case fatality rate was about 80%, despite maximal conservative therapy [9,10].

Several conservative treatment strategies have been proposed to limit brain tissue shifts and reduce intracranial pressure, such as sedation with barbiturates or propofol, hyperventilation, and osmotic therapy with glycerol, mannitol, or hypertonic saline hydroxyethyl starch (HES) [11-13]. However, no trials have addressed the efficacy of these therapies to improve clinical outcome [14], and several reports suggest that these are ineffective [9,10,15] or even detrimental [16,17]. The value of ICP monitoring has also not been established. ICP monitoring may reduce iatrogenic errors [18], but is probably not helpful in guiding long-term treatment [5]. Despite this lack of evidence hyperventilation, osmotherapy, and the use of ICP monitors are recommended and used by experts for patients with ischaemic stroke whose condition is deteriorating secondary to oedema formation [11,12,19].

Because of the limitations of medical therapies, there have been proposals for decompressive surgery in patients with neurological deterioration due to large hemispheric infarction and oedema. The rationale of this therapy is to prevent brain tissue shifts and to normalise intracranial pressure, and thereby to preserve cerebral blood flow and to prevent secondary damage [19]. The technique of decompressive surgery is relatively simple and consists of a large hemicraniectomy and a duraplasty. It can be performed in every neurosurgical centre.

Animal studies have shown that decompressive surgery reduces mortality and improves histological and functional outcome [20,21]. Case reports and small retrospective studies have suggested that this intervention lowers mortality without increasing the rate of severely disabled survivors [19,22,23]. These findings were supported by two prospective series. Mortality was reduced from about 80% in controls to 34% and 16% in surgically treated patients, respectively, and poor functional outcome from 95% to 50% [24,25]. Reports from other studies suggest that decompressive surgery is less effective in elderly patients [26,27], and that substantial recovery extends into the second half year and thereafter [28].

Although the above results suggest a very substantial benefit of decompressive surgery, the studies had too many flaws to be readily translated into clinical practice. Most importantly, the groups were not constituted by random selection. The control groups consisted of patients with a significantly higher age, more co-morbidity, and more frequent lesions in the dominant hemisphere than those in the surgical groups [24,25]. In addition, information on functional outcome of the surviving patients was insufficient [24,25].

The aim of the current study is to test if decompressive surgery would improve functional outcome in patients with neurological deterioration due to large hemispheric infarction and oedema, as compared with 'standard' best medical care, on either a stroke unit (SU) or an ICU, in a randomised controlled clinical trial.

## Methods and design

This is a multi-centre, open, randomised treatment trial with masked outcome assessment. Participating centres have adequate experience with the management of acute ischaemic stroke and intensive care treatment of patients with an elevated ICP, and neurosurgical facilities are available on a 24-hours/day basis. The trial protocol has been approved by the medical ethical committees of all participating centers.

### Enrollment criteria

Patients can be enrolled in the study if they have 1. a diagnosis of acute ischaemic stroke in the territory of the middle cerebral artery, with an onset within 96 hours prior to the planned start of the trial treatment. Within this timeframe, it is advised to start treatment as soon as possible; 2. a score on the National Institutes of Health Stroke Scale (NIHSS) [29] ≥ 16 for right-sided lesions or ≥ 21 for left-sided lesions; 3. a gradual decrease in consciousness to a score of 13 or lower on the Glasgow Coma Scale (GCS) for right-sided lesions, or an eye and motor score of 9 or lower for left-sided lesions; 4. hypodensity on CT involving two thirds or more of the territory of the middle cerebral artery (MCA), and space-occupying oedema formation. (displacement of midline structures on CT is not a requirement for inclusion); and 5. age 18 up to and including 60 years. In addition, there must be a possibility to start trial treatment within 3 hours after randomisation, and written informed consent must be obtained from a representative of the patient.

Patients will be excluded from the study if they have 1. ischaemic stroke of the entire cerebral hemisphere (anterior, middle, and posterior cerebral artery territories); 2. a decrease in consciousness at least partially explained by a cause other than oedema formation, such as metabolic disturbances or medication; 3. two fixed dilated pupils; 4. been treated with a thrombolytic agent in the 12 hours preceding randomisation; 5. a known systemic bleeding disorder; 6. a pre-stroke score on the modified Rankin Scale (mRS) [30] of more than 1 or on the Barthel Index (BI) of less than 95 [31], 7. a life expectancy < 3 years, or 8. a serious illness that may confound treatment assessment.

### Informed consent

Written informed consent for this study will be obtained from the patient's authorised representative prior to the performance of any protocol-specific procedure. However, several of these assessments or tests may be performed as part of the patient's routine clinical evaluation (i.e. not specifically performed for this trial). The study will be conducted in accordance with the provisions of the Declaration of Helsinki, as amended in South Africa (1996).

### Treatment allocation

After informed consent is obtained, patients will be randomised to either surgical or conservative treatment. Randomisation will be stratified for the intended mode of conservative treatment (intensive care or stroke unit care; see below). The choice of conservative treatment is left at the discretion of the local investigator, and will usually be the standard mode of treatment in the participating centre. Allocation to treatment will be made via a telephone call to a 24 hour randomisation service. Ideally, each treatment arm will consist of 56 patients. The total number of patients included in the trial will be 112.

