### IIb. stroke unit care

The patient will be admitted to a stroke unit or medium care unit and is treated according to local practice, supplemented with the treatment options that can be performed in a medium care unit as described above under 'a'.

Treatment strategy 'I' is the experimental option, strategy 'IIa' is recommended by international experts, and strategy 'IIb' is the most common clinical practice in the Netherlands, and probably also in a significant number of other European countries.

The choice of ancillary care measures, e.g., prophylactic administration of (low-molecular-weight) heparin and the treatment of complicating illnesses, will be at the discretion of the treating physician. However, administration of low-dose aspirin is recommended, whereas treatment with intravenous heparin and haemodilution with plasma expanders are discouraged.

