### Statistical aspects

In the primary analysis, outcome of all patients in the surgical group will be compared with that of all patients in the conservative treatment group. However, subgroup analyses will be performed based on the mode of conservative treatment (intensive care vs. stroke unit care), side of the lesion, and time of randomisation (within 48 hours versus between 48 and 96 hours). The sample size is based on the desire that in each of the two subgroups the superiority of surgical decompression over conservative treatment can be proved. All primary analyses will be performed on an intention-to-treat basis, but additional on-treatment analyses will also be performed. An interim analysis will be performed after the one-year follow-up of the first 30 patients.

Power calculations are hampered by the scarcity of data on clinical outcome in this patient group. In the non-randomised trial by Rieke et al., which is most comparable to the proposed study regarding patient group and treatment, 95% (20/21) of the patients in the IC treatment group had a poor outcome, compared with 50% (16/32) in the surgically treated group [24]. There are no data on outcome after 'standard' treatment, but this is not likely to be better than IC treatment. Based on an α of 0.05 and a β of 0.20, extrapolation of these data suggests that only 12 patients would have to be included in each group to demonstrate the superiority of surgical decompression over conservative treatment in a randomised trial. Assuming that 60% of the patients in the surgery group will have a poor outcome and 85% of the patients in each of the two conservative treatment subgroups, a group size of 28 patients would suffice to prove the superiority of decompressive surgery (table 1). Results of applying the same assumption to the complete treatment groups are shown in table 2.

**Table 1 T1:** Results expected for each of the two treatment arms assuming 60% poor outcome after surgery and 85% poor outcome after conservative treatment

	surgery n = 28	conservative treatment n = 28
Poor outcome (n)	17	24
RR (95% CI)	0.71 (0.51–0.99)	ref

RR denotes relative risk; CI, confidence interval. Conservative treatment indicates IC or SU treatment.

**Table 2 T2:** Results expected for the complete treatment groups assuming 60% poor outcome after surgery and 85% poor outcome after conservative treatment

	surgery n = 56	conservative treatment n = 56
Poor outcome (n)	34	48
RR (95% CI)	0.71 (0.56–0.90)	ref

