In the Heidelberg studies, complete global aphasia was an exclusion criterion for decompressive surgery, and the majority of patients receiving surgical therapy had a lesion in the right hemisphere [24,25]. In our study, patients with a large infarct in the dominant hemisphere and severe aphasia may be included, as it is unproven that they will fare worse than patients with an infarct in the non-dominant hemisphere. In fact, it has been shown that with the exception of the ability to communicate, the long-term quality of life of patients with left-sided lesions is slightly better than that of patients with a lesion in the right hemisphere [42].

In this trial, a fully blinded evaluation of the functional outcome of patients is virtually impossible, as patients in the decompressive surgery group will be easily recognised by surgical marks. Even in case of follow up by telephone, patients are likely to note the sequels of surgery. However, sufficient blinding will be assured by the indirect assessment of scores on the functional outcome scales, as described above.

The trial started 1 September 2002. As of 1 July 2006, 52 patients were included in seven participating centres in the Netherlands. Two other Dutch centres and seven centres in the UK are expected to join the trial shortly. Other centres that have adequate experience with the management of acute ischaemic stroke and intensive care treatment of patients with an elevated ICP, and that have neurosurgical facilities available on a 24-hours/day basis are welcome to participate.

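### The 112 patients are justified by proving superiority in each conservative-care stratum with 28 per arm, but the design does not fix stratum size, and 28 per arm gives only about 57% power even at an even split

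*Protocol article*

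**What the plan says.** All references are to the protocol article.

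- **Basis of the sample size** (Statistical aspects): "The sample size is based on the desire that in each of the two subgroups the superiority of surgical decompression over conservative treatment" can be shown. The two subgroups that enter the calculation are the intensive care (IC) and stroke unit (SU) strata.
- **Assumptions** (same section): "Assuming that 60% of the patients in the surgery group will have a poor outcome and 85% of the patients" in each conservative subgroup. On that basis "a group size of 28 patients would suffice to prove the superiority of decompressive surgery (table 1"). Table 1 gives the expected relative risk (RR) as "0.71 (0.51–0.99"). Two strata of 28 + 28 make 112.
- **Error rates** (same section): "Based on an α of 0.05 and a β of 0.20" introduces the preceding calculation of 12 per group. It is not explicitly attached to the 28.
- **What enrolment fixes** (Treatment allocation): a total of 112 and, ideally, 56 per arm. Randomisation is stratified by intended conservative care, but "The choice of conservative treatment is left at the discretion of the local investigator, and will usually be the standard mode of treatment in the" centre. No size per stratum is given.
- **Primary analysis** (Statistical aspects): all surgical against all conservative patients. The comparison by mode of conservative care is listed among the subgroup analyses.
- **Context**: "strategy 'IIb' is the most common clinical practice in the Netherlands" (section IIb), and by July 2006 "52 patients were included in seven participating centres in the Netherlands" (Discussion). Further Dutch centres and seven UK centres were expected to join.

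**The concern.** The article gives the trial a property that its design does not have. Stratified randomisation balances surgery and control within a stratum, but it does not determine how many patients the stratum receives. With only the total fixed and the stratum left to local choice, 28 per arm in both strata is one possible result among many. Table 1 leaves almost no slack, since its upper limit is already 0.99.

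There is a second and larger weakness. An expected interval that just excludes 1 corresponds to a power only a little above one half, so 28 per arm falls well short of proof even when the strata are equal.

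At stake is the reading of the stratum results. A reader who believes that each stratum was sized to prove superiority may take an inconclusive IC or SU result as evidence that surgery does not help against that mode of care, when the stratum was simply too small.

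**Working it through.** **Inputs** (Statistical aspects and Treatment allocation): poor outcome 60% with surgery and 85% with conservative care; 28 per arm per stratum; total 112. Equal arms within a stratum are assumed. The sidedness of the test is not stated; two-sided 5% is assumed, which matches the 95% intervals in the tables.

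**1. Reproduce the tables.** With a and b events in n patients per arm, RR = a/b, SE(log RR) = √(1/a − 1/n + 1/b − 1/n), and the limits are RR × exp(±1.96 SE).

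- Table 1: 17/28 vs 24/28 gives RR 0.708, SE 0.170, interval 0.507 to 0.989. This agrees with the printed figures.
- Table 2: 34/56 vs 48/56 gives 0.708 (0.559 to 0.897). This also agrees.

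**2. Expected interval when the stratum is smaller.** With proportions of exactly 0.60 and 0.85, RR = 0.60/0.85 = 0.706 and SE = √[0.40/(0.60n) + 0.15/(0.85n)].

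| Per arm, smaller stratum | Patients, larger : smaller | Expected 95% interval |
|---|---|---|
| 28 | 56:56 | 0.50 to 0.99 |
| 27 | 58:54 | 0.50 to 0.998 |
| 26 | 60:52 | 0.50 to 1.005 |
| 22 | 68:44 (about 60:40) | 0.48 to 1.04 |
| 17 | 78:34 (about 70:30) | 0.46 to 1.09 |

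The last split with an upper limit below 1 is 58:54, about 52:48.

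**3. Sensitivity to whole patients.** The expected counts at 26 per arm are 15.6 and 22.1, which cannot occur. Neighbouring whole counts give upper limits of 1.027 (16 vs 22), 0.985 (15 vs 22) and 0.972 (16 vs 23). At the planned 28 per arm, 17 vs 23 gives 1.043. The break-even can therefore move by a patient or two and should not be read as a sharp threshold.

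**4. Power.** Method: sum the binomial probabilities of all outcomes in which the two-sided 5% chi-square test without continuity correction is significant, at 60% vs 85%. The strata are independent, so the chance that both are significant is the product.

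| Per arm, smaller + larger | Power, smaller | Power, larger | Both significant |
|---|---|---|---|
| 28 + 28 | 57% | 57% | 32% |
| 26 + 30 | 55% | 60% | 33% |
| 22 + 34 | 47% | 67% | 31% |
| 17 + 39 | 36% | 72% | 26% |

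For example, 0.5695 × 0.5695 = 0.324 at an even split and 0.4658 × 0.6666 = 0.310 at about 60:40. The pooled comparison at 56 per arm has power of about 86%.

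**5. Size needed per stratum.** By the normal approximation without continuity correction, 80% power for 85% vs 60% needs 49 per arm two-sided, or 39 one-sided. At 28 per arm the same approximation gives 56% two-sided and 68% one-sided, so a one-sided test would not make 28 sufficient either.

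**The case against.** The strongest reply is that imbalance hardly affects the stated wish. That wish concerns both strata, and what the smaller stratum loses the larger one gains: the chance that both are significant is 32% at 50:50, 33% at 60:52 and 31% at about 60:40. This stands. A reader might infer that an uneven split makes the aim fail by design; the figures do not support that. The aim has about a one-in-three chance with perfect balance, so the main cause is the 28 per arm. Imbalance matters chiefly for the precision and power of the smaller stratum.

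Other limits also stand:

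- Table 1 shows expected results. A reader might take an upper limit below 1 as a formal success criterion, but the article sets none.
- Proof in each stratum is the reason given for the sample size. It is not the trial's aim, which the Background states against medical care on either type of unit. The primary analysis is pooled and the split does not touch it.
- A reader might infer that the IC stratum will be the smaller one. The article reports no stratum counts. National habit need not describe centres selected for intensive care experience and round-the-clock neurosurgery, and UK centres were about to join. Imbalance is possible; its direction is not established.
- A reader might equate stratum with centre. The article says only that the choice will usually follow local standard care.

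The full protocol may contain a recruitment target per stratum, and its absence from an article is not the point. What remains is a stated claim, that 28 per arm is enough in each stratum, which the stated allocation rule does not deliver and the stated assumptions do not support.

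**Conclusion.** The point holds as a correction to what the article claims, not as a threat to its primary result. The 28 per arm per stratum is conditional on a nearly even split that nothing in the stated enrolment rule secures. Even when the condition is met, power is about 57% per stratum and about 32% for both. At about 60:40 and 70:30 the smaller stratum falls to about 47% and 36%, with expected upper limits of 1.04 and 1.09.

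These figures rest on the plan's own 60% and 85%, equal arms within strata, the same effect in both strata, and a two-sided 5% test. The pooled comparison keeps about 86% power whatever the split.

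**What to change.** In Statistical aspects, and for consistency in Treatment allocation:

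1. Drop the statement that 28 per arm is enough to prove superiority in each stratum, and say that 28 per arm assumes an even split.
2. Give the per-stratum power and expected interval at three splits: 57% and 0.50 to 0.99 at 50:50; for the smaller stratum, 47% and 0.48 to 1.04 at about 60:40, and 36% and 0.46 to 1.09 at about 70:30.
3. Name the pooled comparison, which is already the primary analysis, as the only confirmatory claim. Justify the 112 by its power of about 86%.
4. Report the IC and SU strata as estimates with confidence intervals.

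The cost is a change of wording. No extra patients and no stratum quota are needed; a quota alone would not secure the aim, because the power is too low even at perfect balance. A running stratum count from the existing randomisation service is an optional operational aid. The real price is giving up the promise of proof in each stratum.

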### I. decompressive surgery

Decompressive surgery will consist of a large hemicraniectomy and a duraplasty. In summary, a large (reversed) question mark-shaped skin incision based at the ear will be made. A bone flap with a diameter of at least 12 cm (including parts of the frontal, parietal, temporal, and occipital squama) will be removed. Additional temporal bone will be removed so that the floor of the middle cerebral fossa can be explored. The dura will be opened and an augmented dural patch will be inserted. The dura will be fixed at the margins of the craniotomy to prevent epidural bleeding. The temporal muscle and the skin flap will then be re-approximated and secured. Infarcted brain tissue will not be resected. A sensor for registration of intracranial pressure may be inserted. In surviving patients, cranioplasty will be performed after at least six weeks, using the stored bone flap or acrylate. After surgery, patients will be transferred to an IC unit. Anti-oedema therapy as described under 'IIa' may be used but will usually not be necessary.

### IIa. intensive care

Because no mode of IC treatment has been proven superior to the others, treatment options may vary depending on local traditions. However, to improve consistency of treatment between centres, the following treatment modalities are recommended:

*a. Osmotherapy*. Osmotherapy should be started as soon as possible after randomisation. The use of mannitol or glycerol is recommended in a dose sufficient to reach a serum osmolality of 315 to 320 mOsm.

*b. Intubation *and mechanical ventilation. Patients will be intubated if the score on the GCS is lower than or equal to 10, or if there are signs of respiratory insufficiency, such as a pO2 ≤ 60 mm Hg, a pCO2 ≥ 60 mm Hg, or if the airway is compromised. However, earlier intubation is left at discretion of the treating physician. Mechanical ventilation with use of intermittent mandatory or assist/control ventilation will often be sufficient, especially in the early phase.

*c. Hyperventilation*. The use of hyperventilation is discouraged. If hyperventilation is started, it is advised to monitor venous oxygen saturation with jugular bulb oxymetry and to maintain oxygen saturation higher than 50%. If venous oxygen saturation is not monitored, the pCO2 may be reduced to 28 – 32 mm Hg.

*d. ICP monitoring*. Invasive monitoring of the intracranial pressure is left at the discretion of the treating physician. If used, the ICP monitor should preferably be inserted ipsilateral to the side of the infarct.

*e. Sedation*. If mechanical ventilation requires sedation, and in the case of further neurological deterioration, or an uncontrolled increase in ICP, patients may be sedated with propofol. The use of barbiturates is discouraged, because this may reduce cerebral perfusion pressure and does often not lead to a sustained control of ICP. If necessary, muscle relaxants may be used.

*f. Blood pressure control*. In general, spontaneous elevation of blood pressure to a level of 220/120 mm Hg should be accepted. Sustained higher blood pressures can be treated with labetolol or nitroprusside. In case of sustained hypotension or a critical reduction of cerebral perfusion pressure catecholamines may be used.

*g. Elevation of the head *(30°) to optimise venous drainage.

*h. Aim for normothermia*. Antipyretics and a cooling blanket may be used.

*i. Aim for normoglycaemia*. Consider the use of insulin.

IC treatment should be continued at least until day 5 after stroke onset, or until there is clinical or radiological improvement deemed to be sufficient to transfer the patient back to the stroke unit or medium care unit.

